### Data collection

Patients’ demographic data will be collected at the inclusion assessment (height, weight, age, sex, and ASA classification). The attending anesthesiologist will collect data with regard to the anesthesia and surgical procedure. Nurses will collect the data in the PACU. When the patient is transferred to the orthopedic ward, the Acute Pain Service Team will score the QoR-40 on postoperative days 1 and 3, adjust analgesia when necessary, and systematically screen for side effects. Ward nurses will assess NRS pain scores in the morning and evening on postoperative days 1–3. Morphine patient-controlled analgesia (PCA) consumption will be electronically registered by the PCA pump; all other data will be registered by nurses of the PACU, ward pain department, or trial nurses. All medication can be retrieved from the patient data management systems. Complications will be assessed on the day of discharge. During the 72 h of the trial, data will be registered on paper. After termination of the trial (72 h after surgery), the data will be directly registered in the software program Open Clinica.

An independent trial monitor from the Clinical Trial Center at Antwerp University Hospital will conduct a follow-up on the GCP performance of the trial in both study locations. All data will be published anonymously.

### Sample size

Our sample size calculation is based on data from a randomized controlled trial comparing the effect of systemic infused lidocaine with placebo on the 24-h morphine requirement in posterior lumbar arthrodesis [11]. We considered a 25% reduction in PCA morphine consumption to be clinically relevant. To calculate the sample size, we assumed a mean of 51-mg morphine with standard deviation of 19 mg (mean morphine consumption for the placebo group of the above-mentioned trial), a type 1 failure risk of 5%, and a type 2 failure risk of 20%. Thirty-five patients are required in each group to detect a 25% reduction in morphine equivalent over 24 h. The sample size calculation was based on an independent samples *t* test. We plan to include 80 patients in total to compensate for potential dropouts and uncertainty in predicting the actual standard deviation.

### Patient characteristics and baseline comparisons

Demographic and other baseline characteristics will be summarized by treatment group. For categorical variables, frequencies and percentages will be reported. Where values are missing, percentages will be calculated for the available cases, and the denominator will be mentioned. Continuous variables will be summarized as mean with standard deviation or median with interquartile range as appropriate.

Comparisons of demographic and baseline characteristics between the treatment groups will be conducted to assess the effectiveness of randomization. For categorical variables, the chi-squared test or Fisher exact test (when numbers are low) will be used. For continuous variables, a *t* test or Mann–Whitney *U* test will be used as appropriate. The following baseline information prior to randomization will be collected: age, sex, BMI, ASA physical status, indication for surgery, preoperative pain (NRS score), and use of analgesics.

### Analysis of the endpoints

SPSS software version 21 (SPSS, Chicago, IL, USA) or 3.3.2 will be used for statistical analysis. The primary endpoint will be analyzed by using an independent samples *t* test intention-to-treat population (in case of normality).

To evaluate the sensitivity of the results of the primary outcome analysis, a linear regression will be used to model the cumulative morphine consumption during the first 24 h after surgery with treatment as predictor and taking into account possible confounders.

A linear mixed model will be used to model the cumulative morphine consumption over time with subject as a random effect. This model allows correction for confounders and adding a random intercept for site. From this model, the difference in morphine consumption at the different time points can be estimated.

To compare the continuous outcomes (intraoperative sufentanil dosage, required morphine dose, pain scores, QoR-40 score, nausea and vomiting score, and number of administered postoperative anti-emetics) at different time points, we will use an independent samples *t* test if they are normally distributed or a Mann–Whitney *U* test if otherwise. We will also fit a linear regression model for these outcomes, which makes it possible to correct for confounders. A linear mixed model will be studied for the continuous outcomes measured over time.

The time to the different events of interest (first mobilization to a chair, first walk of 20 m, first meal, and first defecation) will be studied in a time-to-event analysis comparing the two treatment arms. We will use a Cox proportional hazard model to adjust for other variables if necessary.

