### Randomization

Patients will be assigned consecutive numbers upon inclusion in the study. These numbers are randomly allocated (1:1) to the ESB or the sham group by using a web-based randomization system, QMinim. QMinim uses stratified randomization, and stratification will be carried out according to site, gender, and levels of surgery. In QMinim, a minimization procedure is used to randomly assign the patients to ensure a similar distribution of the stratifying arms. Online randomization will be carried out by an independent anesthetist who will also prepare the medication.

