### Primary endpoint

The primary endpoint is the morphine consumption during the first 24 h postoperatively in milligrams and will be determined from the PCIA pump.

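### The primary t test ignores the factors used in the minimisation and depends on a normality check; one adjusted linear model, fixed in advance, would be better at almost no cost

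*Protocol article*

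**What the plan says.** Under Randomization, allocation is 1:1 and "stratification will be carried out according to site, gender, and levels of surgery". The method is minimisation: "In QMinim, a minimization procedure is used to randomly assign the patients to ensure a similar distribution of the stratifying arms".

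Under Primary endpoint, the outcome is continuous: "The primary endpoint is the morphine consumption during the first 24 h postoperatively in milligrams and will be determined from the PCIA pump".

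Under Analysis of the endpoints, "The primary endpoint will be analyzed by using an independent samples" t test in the "intention-to-treat population (in case of normality"). That sentence gives no criterion for normality and no alternative test. The same section then plans:

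- a linear regression of 24-h morphine as a sensitivity analysis, adjusted for confounders that are not named;
- a mixed model for cumulative morphine over time, which may include a random intercept for site;
- for a list of continuous outcomes, a t test or, if the data are not normal, a Mann–Whitney U test. The list includes an entry for required morphine dose.

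No section commits the primary analysis to the three minimisation factors.

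**The concern.** There are two linked issues.

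**Analysis and design do not match.** Minimisation balances site, gender and levels between the arms, so variation due to these factors largely drops out of the treatment difference. The two-sample t test still counts it as noise. If the factors are prognostic, the confidence interval is wider than the design warrants, the test rejects too rarely under the null, and some power is lost.

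**The primary test depends on the data.** The t test applies only if the observed data look normal. If they do not and Mann–Whitney U takes over, the trial no longer tests a mean difference in mg. That difference is what the Sample size section planned for: 51 mg, SD 19 mg and a 25% reduction, using an independent samples t test.

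**Working it through.** **Inputs from the Sample size section.** Control mean 51 mg, SD 19 mg, difference 0.25 × 51 = 12.75 mg, alpha 5%, power 80%, 35 per group required, 80 patients in total (40 per arm).

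**Assumed input.** R², the share of outcome variance explained by the three minimisation factors. The documents do not give it; 0, 0.10 and 0.20 are shown.

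**1. The plan's own figure.** n = 2(1.96 + 0.8416)² × 19² / 12.75² = 34.86, so 35 per group. The stated number reproduces with a two-sided test; one-sided gives 28. With 40 per arm, unadjusted power at R² = 0 is 84.2% (noncentral t) or 85.1% (normal approximation).

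**2. Standard error.** The t test uses 19 × √(2/40) = 4.25 mg. With the factors balanced, the true SD of the difference is 4.25 × √(1 − R²), so the standard error is too large by the factor 1/√(1 − R²):

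- R² = 0.10: 1.054, about 5% too large
- R² = 0.20: 1.118, about 12% too large

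**3. Type I error of the t test.** 2 × [1 − Φ(1.96/√(1 − R²))]:

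- R² = 0.10: 3.9%
- R² = 0.20: 2.8%

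**4. Power of the t test under minimisation.** The critical difference is 1.99 × 4.25 = 8.46 mg. Power is about Φ[(12.75 − 8.46)/(4.25√(1 − R²))]:

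- R² = 0.10: Φ(4.29/4.03) = 85.7%
- R² = 0.20: Φ(4.29/3.80) = 87.1%

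**5. Power after adjustment.** Noncentral t with SD 19√(1 − R²): 87.8% at R² = 0.10 and 91.2% at R² = 0.20.

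**6. Simulation.** N = 80, minimisation on three assumed 50/50 binary factors with a 0.8 biased coin, 3,000 trials per setting:

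| R² | t-test SE vs true SD (mg) | Type I: t test / adjusted | Power: t test / adjusted |
|---|---|---|---|
| 0 | 4.23 vs 4.17 | 4.6% / 4.4% | 84.0% / 83.8% |
| 0.10 | 4.25 vs 4.02 | 3.9% / 5.0% | 86.0% / 88.5% |
| 0.20 | 4.24 vs 3.82 | 2.8% / 4.7% | 86.4% / 91.2% |

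Monte Carlo error is about 0.4 points for type I error, √(0.05 × 0.95/3000), and about 0.6 points for power. At R² = 0 the two standard-error figures agree within simulation error. The formulas and the simulation together put the gain in power at about 2 to 5 points.

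**7. The normality condition.** The article names no check, so Shapiro–Wilk at 5% in either arm is assumed, with Mann–Whitney U as the fallback (40 per arm, 4,000 trials per setting). For scale, a lognormal with mean 51 and SD 19 has sigma = √ln(1 + (19/51)²) = 0.36.

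| Assumed shape | Check rejects normality | t-test type I | Check-then-test type I | Smaller of two p values, type I | Verdicts differ at 12.75 mg |
|---|---|---|---|---|---|
| Normal | 9% | 5.4% | 5.5% | 6.1% | 4.0% |
| Lognormal, sigma 0.3 | 73% | 4.7% | 5.2% | 6.0% | 5.8% |
| Lognormal, sigma 0.5 | 98% | 4.9% | 5.3% | 6.8% | 9.7% |

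The t test holds its level under this skew, so the check adds no protection. With moderate skew it would usually replace the planned test.

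**The case against.** **The error is conservative and its size is unknown.** Type I error is not inflated, the sample size reproduces, and the planned test is the one the trial was sized on. At R² = 0 there is no loss. All of this stands, and it limits the weight of the point.

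**Adjustment is already planned.** There is a sensitivity regression and a mixed model, and a covariate list is commonly left to the SAP. That stands as to unnamed confounders. It does not change the fact that the article states the primary method, and that method is unadjusted.

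**A fallback arguably exists.** A reader might infer that no test is given for non-normal data. The Mann–Whitney alternative may reach the primary endpoint through the entry for required morphine dose. Even so, the data would decide, with no stated criterion.

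**The data-dependence does little harm.** A check applied mechanically keeps type I error near 5%, and even free choice of the smaller p value gives only 6.0–6.8%. The Blinding section holds unmasking until the analysis is complete, which limits choice by direction. This largely stands.

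**Mann–Whitney can be more powerful under skew.** In the simulation, for a pure 12.75 mg shift, it reached 88.2% against 84.8% at sigma 0.3, and 94.3% against 85.1% at sigma 0.5. That could justify choosing a rank test in advance. It does not justify letting a normality check choose, and a rank test does not estimate the mean difference in mg.

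**Two stronger readings fail.** A reader might infer that baseline significance tests will select the covariates. The article says only that "Comparisons of demographic and baseline characteristics between the treatment groups will be conducted to assess the effectiveness of randomization"; it does not link them to any model. A reader might also set adjusted power of 88% or 91% against 84%. But 84% is the t test's power at R² = 0. At the same R², minimisation raises the t test's own power to about 86–87%.

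**Conclusion.** The point holds as a modest improvement that should be made. The primary analysis ignores the factors used in allocation. To the extent that they are prognostic, it overstates the standard error: by about 5–6% at R² = 0.10 and 11–12% at R² = 0.20, with type I error of about 3.9% and 2.8%. Adjustment raises power at 40 per arm from about 86% to 88%, or from 86–87% to 91%. These figures rest on assumed R² values; at R² = 0 there is neither loss nor gain, and at 40 per arm power exceeds 80% with either analysis.

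The normality condition leaves the primary test open to the data and may change what is estimated, without improving type I error control at this sample size. The rates at which the check rejects depend on the assumed check and distributions.

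Nothing here shows an inflated false-positive rate, a wrong sample size or an invalid trial.

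**What to change.** State one primary analysis under Analysis of the endpoints: a linear regression of 24-h morphine consumption (mg) on treatment, site, gender and levels of surgery in the intention-to-treat population, fitted whatever a normality check shows. Report the adjusted mean difference with its 95% confidence interval. Keep the independent samples t test and the Mann–Whitney U test as named sensitivity analyses.

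Further covariates, such as age or preoperative pain score, and robust standard errors are optional; the point does not depend on them.

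The cost is one paragraph of wording. With two hospitals and one or two surgical levels, the model adds three parameters, so residual degrees of freedom fall from 78 to 75 at N = 80. No new data or patients are needed, and the change should be made before unmasking.

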### Objectives and purpose

In this prospective, randomized, double-blind placebo-controlled clinical trial, we will investigate the effect of bilateral ESB (20 mL of levobupivacaine 0.25%) on 24-h postoperative morphine consumption when compared with a sham block (20 mL of NaCl 0.9%) following posterior lumbar inter-body fusion surgery. Secondary objectives include the effect of the ESB on the numeric rating scale (NRS) pain scores in rest at fixed time points: at the time of inclusion, in the post-anesthesia care unit (PACU) (T0 = arrival in PACU, T + 15 min, T + 30 min), and on the ward (twice daily: morning and evening until postoperative day 3). Other secondary objectives are the effect of an ESB on the NRS pain scores during defined movement (mobilization to chair) at 24 h, 48 h, and 72 h; time to first mobilization to chair (hours); time to first walk of 20 m (hours); the required sufentanil dose during surgery (micrograms), total morphine consumption during the first 72 h postoperatively (milligrams), and the Quality of Recovery 40 survey (QoR-40) score at days 1 and 3.

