### Secondary endpoints

As secondary endpoint, the total morphine consumption in milligrams, during the first 72 postoperative hours, will be extracted out of the PCIA pump. Pain scores at rest will be assessed with the NRS score (0 = no pain, 10 = worst imaginable pain) and tested at regular time intervals: at the time of inclusion, in the PACU (T0 = arrival in PACU, T + 15 min, T + 30 min), and on the ward (twice daily: morning and evening until postoperative day 3). Pain scores during defined movement (first moving to a chair and sitting upright) will be registered. Time to first mobilization to a chair (in hours since T0) and time to first walk of 20 m (in hours since T0) will be noted in the patients’ study diary. The QoR-40 score will be calculated from the responses to a standard questionnaire at postoperative days 1 and 3. The QoR-40 is a widely used and extensively validated measure of quality of recovery. It is a 40-item questionnaire on quality of recovery from anesthesia that has been shown to measure health status after surgery [9, 10].

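### Pain scores get three unranked analyses, and the pre-block inclusion score is listed as an effect time point without being named as a covariate

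*Protocol article*

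**What the plan says.** Analysis of the endpoints gives three methods for pain scores in one paragraph.

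- **Tests by time point.** The list of outcomes begins "To compare the continuous outcomes (intraoperative sufentanil dosage, required morphine dose, pain scores, QoR-40 score, nausea and vomiting score". These are compared "at different time points, we will use an independent samples *t* test if they are normally distributed or a Mann–Whitney *U* test if otherwise".
- **Regression.** "We will also fit a linear regression model for these outcomes, which makes it possible to correct for confounders". The confounders are not named.
- **Mixed model.** "A linear mixed model will be studied for the continuous outcomes measured over time". Its fixed effects and the role of the baseline score are not given.

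No order is stated among the three. For the primary endpoint the same section does give one: the t test is the analysis and the regression is there to assess sensitivity.

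The pain schedule is spread over three sections. Secondary endpoints lists rest pain "at the time of inclusion, in the PACU (T0 = arrival in PACU, T + 15 min, T + 30 min"), followed by the ward. Data collection adds "Ward nurses will assess NRS pain scores in the morning and evening on postoperative days 1–3". Objectives and purpose adds "NRS pain scores during defined movement (mobilization to chair) at 24 h, 48 h, and 72 h".

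The inclusion score has two roles. Objectives and purpose places it in the list of times for the effect of the block: "pain scores in rest at fixed time points: at the time of inclusion, in the post-anesthesia care unit (PACU"). Patient characteristics and baseline comparisons lists preoperative NRS pain as information collected before randomization, and the use stated there is a comparison between the groups.

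**The concern.** When three analyses of the same scores have equal standing, the one that is reported can be chosen after the results are seen. The tests by time point add a second choice, of which time to emphasise. The t or Mann-Whitney decision may also differ from one time to the next.

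The inclusion score raises a separate problem. Patients are recruited at the preoperative consultation and the block is given later, so this score cannot show an effect of the block. A group difference there is chance. The useful role for the score is as a covariate for later pain, and the text does not assign it that role.

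At stake are the credibility of the pain results and some of their precision. The 24-h morphine result is not affected.

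**Working it through.** The protocol states no figure for the pain analysis, so there is none to reproduce.

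**Number of tests**

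| Pain score | Times | Source |
|---|---|---|
| Rest, PACU | 3 | Secondary endpoints |
| Rest, ward | 2 × 3 days = 6 | Data collection |
| Movement | 3 | Objectives and purpose |
| Total after the block | 12 | |

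The inclusion score would be a thirteenth.

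**Chance of at least one p < 0.05 when the block has no effect on pain**

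If the tests are independent: 1 − 0.95^12 = 0.460.

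Repeated scores in the same patients are correlated, so independence is an upper reference. The protocol gives no correlation. The values below come from simulating equally correlated standard normal test statistics (200,000 runs, |z| > 1.96).

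| Assumed correlation | 12 tests |
|---|---|
| 0 | 46.0% |
| 0.3 | 39.6% |
| 0.5 | 31.7% |
| 0.7 | 23.1% |
| 0.9 | 13.5% |

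Secondary endpoints describes movement pain as the first move to a chair, which could be read as a single score. That reading leaves 3 + 6 + 1 = 10 tests: 1 − 0.95^10 = 40.1% if independent, 28.6% at 0.5 and 12.8% at 0.9. The conclusion does not change.

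**Precision from adjusting for inclusion NRS**

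The residual variance is multiplied by 1 − ρ², where ρ is the correlation between the inclusion score and a later score. The protocol does not give ρ.

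- ρ = 0.3: 1 − 0.09 = 0.91, a 9% cut. Interval width is multiplied by √0.91 = 0.954, about 5% narrower.
- ρ = 0.5: 1 − 0.25 = 0.75, a 25% cut. Interval width is multiplied by √0.75 = 0.866, about 13% narrower.

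**Role of the inclusion score**

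Objectives and purpose treats it as a time for assessing the effect. Secondary endpoints lists it in the same schedule as the post-block scores. Patient characteristics and baseline comparisons treats preoperative NRS pain as a pre-randomization characteristic. A pre-block measurement can serve only in the last of these roles.

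**The case against.** Four arguments weigh against the point.

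1. **The plan is not limited to unadjusted tests.** A reader might infer that pain is analysed only by separate tests. The text does not support this: the next two sentences add a regression that can be adjusted and a longitudinal model. A reader might also infer that baseline pain is excluded as a covariate. It is not. The confounders are simply unnamed, and a statistical analysis plan that is not shown may name them. Both corrections stand. What remains is that the article commits to the tests by time point and sets two further models beside them without a ranking.

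2. **The inclusion time is loose wording.** In Secondary endpoints it reads as an assessment schedule, and no claim of an effect at inclusion is made. A longitudinal model may also keep the baseline score among the responses with group means constrained to be equal. That is fair, but Objectives and purpose does place the score under the effect of the block, and even the constrained model estimates no effect at baseline.

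3. **The consequences are modest.** The error rates are all below one half, 46% assumes independence, and the precision gain rests on an assumed correlation. Pain is a secondary outcome. All of this stands and limits the weight of the point.

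4. **The mixed model needs care.** An unstructured covariance over nine rest times has 9 × 10 / 2 = 45 parameters with 80 patients. An overall effect depends on how times are weighted, since three of the nine rest scores fall in the first 30 minutes in PACU. Averaging over three days could dilute a short-lived effect of a single injection. These points stand, so the contrast and a covariance fallback must be stated in advance and the time-specific estimates kept.

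**Conclusion.** The point holds as a matter of unranked analyses and a misplaced baseline score. Under per-time testing as written, the chance of at least one false positive over 12 post-block pain tests is about 13% to 46%, depending on correlations that the protocol does not give. Every value in that range is well above 5%. The precision available from adjusting for inclusion NRS is a 9% to 25% cut in residual variance if the correlation is 0.3 to 0.5, which is an assumption. The calculation takes the preoperative NRS listed as baseline information to be the inclusion score, or an equivalent pre-block score.

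The change is worth making because it uses a score already collected and a model already planned. It concerns secondary outcomes only.

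**What to change.** - Remove the inclusion score from the times at which a treatment effect is assessed, in Objectives and purpose and in Secondary endpoints, and call it a baseline measure.
- Name the planned linear mixed model as the inferential analysis for rest pain and for movement pain, with inclusion NRS and the stratification factors (site, sex, levels of surgery) as covariates.
- Prespecify one treatment contrast over the post-block times for each of the two outcomes, with its weights.
- State the covariance structure and a fallback if the model does not converge.
- Report time-specific differences with confidence intervals as descriptive. The t or Mann-Whitney comparisons may stay if they carry the same label.

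The cost is analysis wording plus the decisions on contrast and covariance. No extra patients or data are needed. Time-specific p values are no longer inferential, which is a small loss.
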